### Aboriginal Oral Health

A recent report on the oral health of school children examined within the School Dental Service (SDS) in WA showed that Aboriginal children had nearly twice the decay experience of non-Aboriginal children in both deciduous and permanent teeth, and 1.8 times and 2.4 times the number of carious deciduous and permanent teeth, respectively, after controlling for exposure to community water fluoridation and socioeconomic level [17]. Also, although the rate of admission for hospital-based care has increased for Aboriginal children and is now approaching the rate of non-Indigenous children, it is lower for Aboriginal children in rural and remote areas. This has been attributed to lack of access to care due to costs, availability of services, and a lower proportion of Aboriginal children with dental insurance [6].

In WA, nearly two-thirds of the Aboriginal population lives in rural and remote locations, making access to services challenging [18]. The WA Aboriginal Health and Wellbeing Framework identified oral health among the priorities addressing risk factors, along with development of health services tailored to meet the needs of the Aboriginal people underpinned by evidence, based on quality research [18]. The proposed research will evaluate a model of care, which can be translated into mainstream health service delivery, using a strong randomized controlled study design.

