### Why is this Study Important?

Provision of dental care to preschool children poses significant challenges because of the stage of development and capacity for cooperation of the young child, and treatment is often provided under GA. The issues are multiplied for Aboriginal preschool children in rural and remote locations where access to specialist dental care is severely limited. Alternative approaches to dental treatment of dental decay in preschool children in primary dental care settings that reduce the need for GA is urgently required. This study will test the hypothesis that Aboriginal preschool children in rural or remote locations can be provided with appropriate dental care using the ART-based approach, without the need for specialist care and can potentially avoid the need for GA.

Our study has six major strengths: (1) it will further develop and evaluate the ART-based model of care, which had been successfully tested in a pilot program in an urban setting in WA, led by author PA, (2) we will develop, for the first time, a dental specific child health utility scale, (3) we will measure the change in clinical parameters as well as the changes in child quality of life and health utility with dental treatment, (4) we will measure the impact of dental treatment on child dental anxiety, (5) we will undertake a cost-effectiveness/cost-utility analysis, and (6) we will ascertain the community acceptability of the tested intervention through focus group interviews. The “holistic” evaluation of the intervention including efficacy and effectiveness of the clinical intervention as well as impact on psychosocial parameters and economic evaluation will greatly facilitate research translation. Also, our research team comprise both world-class researchers who have experience working with the Australian Aboriginal population, and leading policy and service delivery experts, thus ensuring the translation of the study findings into applicable policy, practice, and service delivery in rural and remote locations. We will also be working in collaboration with an Indigenous Advisory Committee and significant community members to provide oral health promotion training to significant community members. This will embed oral health promotion within the communities and ensure sustainability of the oral health improvements after the research has been concluded.

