### Aims

The principal aim of the proposed study is to develop, implement, and evaluate a remote primary care model to deliver effective primary dental services, encompassing treatment and preventive services, to Aboriginal preschool children (based on minimally invasive approaches including ART). This will be compared with standard care for cost and benefits in terms of improved dental health and reduced childhood dental anxiety. Our specific aims and hypotheses are:

Aim 1. Measure the proportion of children able to be provided with care without the need for dental specialist referral and the increment in dental caries. Hypothesis: The proportion of children successfully managed without specialist referral and without new dental caries will be higher in the test group compared with the control.

Aim 2. Develop a dental-specific health utility scale and measure the change in childhood health utility. Hypothesis: The change in health utility will be greater in the test group compared with the control.

Aim 3. Undertake an economic evaluation of the intervention. Hypothesis: The test intervention will have either less costs with greater/similar health gain or affordable incremental costs for additional unit of health outcomes.

Aim 4. Measure the change in childhood oral health-related quality of life. Hypothesis: The child oral health-related quality of life in the test group will be better than the control

Aim 5. Evaluate the acceptability of the ART-based care through focus group interviews. Hypothesis: The ART-based care will have greater acceptability than the control.

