### Recruitment

We will adopt successful recruitment strategies applied in a wide body of research undertaken by author LJ in her work (unpublished) with Aboriginal communities in South Australia and the Northern Territory. This has included extensive engagement with Aboriginal communities and active community participation in the research process. We will engage with community elders through linkages established by authors DA and RM who both have a long association with Aboriginal communities in the Kimberley region. We will employ local Aboriginal people as research assistants to facilitate with community engagement and participant recruitment guided by a senior project officer based in Kimberley. Participant recruitment will be a two-step process: (1) elicit specific communities to participate, and (2) elicit individual participation. A Senior Research Officer appointed to coordinate the project with the assistance of an Aboriginal research assistant will meet with the Chief Executive Officers of individual Aboriginal communities to explain the proposed study to invite community participation in the study. An Aboriginal Advisory Group with representation from all the Aboriginal Controlled Health Organisations in Kimberley will also be formed to provide appropriate guidance to the research team and assist with information dissemination and participant recruitment. Individual participant recruitment will use active engagement with community members at locations where study participants are likely to gather, such as visits to early childhood learning facilities, community general store, local community women’s functions, and through word-of-mouth dissemination of project information. Parents and guardians will provide signed informed consent after being provided with information about the study and the processes undertaken to protect and preserve data confidentiality.

Parents and children aged 0-4 years, residing in selected communities in the Kimberley region of WA will be eligible. Children with complex medical conditions or developmental syndromes would be excluded. All other children within the scope for age and who consent to participate will be recruited.

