### Outcomes

Primary outcomes are specialist referral and the increment in dental caries. Secondary outcomes are quality of life and acceptability of the ART-based care.

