### Economic Evaluations

#### Cost-Effectiveness Analysis

Cost-effectiveness of the intervention will be estimated using standard approaches [36] and will be from a health care provider perspective. Effectiveness measures will be the number of children managed in primary care without need for specialist referral, changes in COHRQoL, the numbers and types of treatments provided, and dental caries increments. The economic evaluation will compare any incremental costs of the intervention (ie, costs accrued in the intervention arm compared to those in the control arm) to the full list of incremental primary and secondary outcome endpoints, all expressed in their natural units of measurement. Costs will be measured from activity data with pathway analysis to fully specify all activities in both intervention and control arms. The resource use and dental services utilization will be obtained from research team records and intervention provider records. Measured resource use will be valued using both existing estimates of the costs of each unit of the resource use from market prices and the Dental Benefit Schedule fee rates for nonspecialist and specialist attendances. Standard discounting will be applied to both cost and outcomes. Uncertainty in the cost and outcome data will be subjected to sensitivity analyses.

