### Treatment Procedures

Test children will be provided with care by dental therapists previously trained in and using the ART approach. Treatment will be undertaken at SDS clinics or field settings, using portable equipment. Restorative treatments will be provided using hand instruments principally, without the use of local anesthesia with the cavity prepared and subsequently restored with a glass-ionomer cement. Where extractions are required, the procedure will be undertaken using standard care approaches. All children will also be provided with preventive fluoride varnish applications at treatment and reviewed at 6-month follow-ups. All treatment will be recorded in patient clinic records. At the 6-month reviews, participants will be provided with preventive fluoride varnish and any other necessary care. Children unable to be provided with care will be referred for specialist care. There will be no direct costs incurred by the participants for the primary care.

Control children will be provided with standard care as part of the fluoride varnish program. Children found to require dental treatment will be referred for care through the prevailing care pathway, that is, government dental services or local private practitioners.

In order to ensure all participants are offered the opportunity to access dental treatment, and in keeping with the delayed treatment intervention design, control participants will be offered treatment using the test treatment approach after the 12-month follow-up.

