### Sample Size

A recently completed pilot study in WA, which compared ART-based care against standard care, reported a nine-fold difference in the proportion of children referred for specialist pediatric dentist care (5% vs 49%). A conservative difference in effect size of 2.5 was assumed to estimate the sample size (10% vs 25%). The intracluster correlation was estimated from the dental caries experience of Aboriginal children participating in a NHMRC Project Grant (1010758)‒funded cluster randomized trial (.05). Using these parameters, with 15 clusters available in each arm of the trial, the estimated sample size required, at 80% power and alpha of .05, was 165 in each arm of the trial with 11 children per cluster. Allowing for loss to follow-up of 25%, the estimated sample size is 220 per arm of the study or 15 children per cluster. The recently completed pilot trial in WA, undertaken by author PA, achieved 90% retention of study participants after 12 months, while an oral health promotion intervention undertaken by author LJ among an Aboriginal population achieved 80% retention of study participants. The estimated sample size will have sufficient power to detect a 33% difference in mean ECOHIS at 90% power and alpha of .05.

The study timeline is shown in Table 2. It is expected that community engagement will take the bulk of the first year in recognition of the challenges of undertaking research in northwestern WA, which is as far as Sydney is from Perth (about 3000 km). Participant recruitment and treatment provision is similarly expected to take up to 2 years because of constraints of locations of communities and weather conditions.

**Table 2 table2:** Study timeline, indicated by actions taken per quarter.

Action	Year 1				Year 2				Year 3				Year 4				Year 5			
	1	2	3	4	1	2	3	4	1	2	3	4	1	2	3	4	1	2	3	4
Community engagement, staff recruitment, training, ethics approval, printing	✓	✓	✓	✓																
Participant recruitment, baseline, examinations, randomization, commence treatment, baseline data entry			✓	✓	✓	✓	✓	✓	✓	✓										
Follow-up examinations, focus group interviews, delayed intervention group treatments							✓	✓	✓	✓	✓	✓	✓	✓	✓					
Data entry, data clean-up, data analyses									✓	✓	✓	✓	✓	✓	✓	✓	✓			
Report preparation, community presentation and feedback																	✓	✓	✓	✓

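### The referral primary outcome is worded inconsistently, and on the wording used to size the trial a control child with decay who never reaches a dentist counts as a favourable result

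*Protocol article*

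**What the plan says.** The referral outcome appears in several forms in the protocol article.

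- Outcomes: "Primary outcomes are specialist referral and the increment in dental caries".
- Sample Size: the trial is sized on the proportion referred, 10% vs 25%, set as a cautious version of the pilot's 5% vs 49%.
- Aims, in the first specific aim: "Measure the proportion of children able to be provided with care without the need for dental specialist referral and the increment in dental caries". The hypothesis under it refers to children successfully managed, with neither a referral nor new caries.
- Data Analysis: Aim one is named as the primary outcome and tested as a proportion. The section does not say which of these forms is meant.

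The route to a referral differs by arm (Treatment Procedures). Test children are offered care by trial dental therapists, who refer to a specialist those they cannot manage. For control children, "Children found to require dental treatment will be referred for care through the prevailing care pathway", that is, to government services or private practitioners.

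The article describes access in this setting as poor. Why is this Study Important? says that "access to specialist dental care is severely limited". Aboriginal Oral Health reports lower hospital dental admission for rural and remote Aboriginal children and adds: "This has been attributed to lack of access to care due to costs, availability of services". Current Situation describes out-of-pocket costs and long travel for preschool children.

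Eligibility does not require caries (Recruitment): "All other children within the scope for age and who consent to participate will be recruited". The pilot rates came from children with early childhood caries (Evidence).

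**The concern.** A specialist referral is recorded only if someone able to refer has seen the child. In the test arm the trial supplies that person. In the control arm the child must first reach an outside service. If the outcome is simply referred or not referred, a control child with untreated decay who is never seen falls in the favourable category.

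A small or reversed difference in referral could then mean that the ART-based model failed, or that control children received no care, and the outcome could not tell these apart. The same ambiguity would pass into the cost-effectiveness ratio, because management without referral is one of its effectiveness measures.

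**Working it through.** **Reproducing the plan's figure.** Inputs from Sample Size: 10% vs 25%, ICC .05, 15 clusters per arm, 80% power, alpha .05 (taken as two-sided).

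- Individually randomised n = 100 per arm.
- Cluster size m = n(1 − ICC)/(k − n·ICC). With k = 15: 95/10 = 9.5, rounded to 10. With one cluster per arm set aside (k = 14): 95/9 = 10.56, rounded to 11, and 11 × 15 = 165.
- A t-based check on 28 degrees of freedom gives 79.8% power at m = 10 and 82.2% at m = 11.
- Loss to follow-up: 165/0.75 = 220.

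The stated 165 and 220 reproduce, so the arithmetic is not at issue.

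**Base for the scenarios.** Design effect = 1 + (11 − 1) × 0.05 = 1.5. Effective n = 165/1.5 = 110 per arm. Power uses the pooled two-proportion formula:

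Φ{ [|p1 − p2|√n − 1.96√(2p̄(1 − p̄))] / √(p1(1 − p1) + p2(1 − p2)) }

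For 10% vs 25%: (1.573 − 1.053)/0.527 = 0.987, so power is 84%.

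**Access.** Let f be the share of control children in need who reach a provider able to refer them. The recorded control rate is then 25% × f, with the test arm held at 10%.

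| f | control | test | difference (control − test) | power |
|---|---|---|---|---|
| 1.0 | 25% | 10% | 15 points | 84% |
| 0.8 | 20% | 10% | 10 points | 55% |
| 0.6 | 15% | 10% | 5 points | 20% |
| 0.4 | 10% | 10% | 0 | none to detect |
| 0.3 | 7.5% | 10% | −2.5 points | reversed |
| 0.2 | 5% | 10% | −5 points | reversed |

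Break-even is f = 0.10/0.25 = 0.40. From the pilot rates it is 0.05/0.49 = 0.10. With those rates f = 0.6 gives 29.4% vs 5% (power above 99%) and f = 0.4 gives 19.6% vs 5% (91%).

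**Children without treatment need.** Let q be the share needing treatment, and suppose 10% and 25% apply only to them. The rates become 10%·q and 25%·q. Power is 73% at q = 0.8, 59% at 0.6, 50% at 0.5 and 41% at 0.4. Both arms shrink by the same factor, so the sign cannot change. Combining the two, q = 0.6 and f = 0.6 gives 6% vs 9% and 13% power.

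**The case against.** **The analysed outcome may already be the better one.** Data Analysis tests Aim one, and Aim 1 requires that care be provided. On that wording an unseen child is not clearly a success. This stands: a reader might infer that the plan definitely scores such children as successes, and the article does not say so. What remains is that Outcomes and Sample Size use the other wording and that nothing settles which governs.

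**Access is part of the intervention.** The model is meant to bring care to remote communities, so an access effect belongs in the contrast. This is fair. But plain referral credits that effect to the wrong arm. Scoring untreated children as non-successes credits it to the test arm, which is why the untreated share must be shown separately.

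**The planning rates already leave room.** The sponsor cut the pilot contrast heavily, and from the pilot rates reversal needs f near 0.10. This also stands. The result depends on the starting rates, and no value of f is documented.

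**Stronger readings that the article does not support.**

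- That the whole primary comparison measures access. Caries increment is also primary, is examined at 12 months in all participants by a blinded examiner, and does not depend on referral.
- That caries-free children can reverse the result. They only dilute it.
- That every test child is seen. Test children are offered appointments, and under intention-to-treat an unseen test child would also be not referred.
- That control referrals will be missed because of the data source. The sentence "The resource use and dental services utilization will be obtained from research team records and intervention provider records" is in the cost-effectiveness section and is not stated for the primary outcome. The same section promises to specify all activities in both arms. The worry is reasonable, since no other referral source is named, but it is an inference.

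The bias runs against the trial's own hypothesis, so a clear referral benefit would not be undermined by it.

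**Conclusion.** The point holds in this form. The referral primary has conflicting wordings, and the one used to size the trial scores an unseen control child with decay favourably. The resulting contrast mixes access with treatment success, biased against the intervention.

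At the planned rates, power is 84% with full access, 55% at f = 0.8 and 20% at f = 0.6. There is no difference at f = 0.4, and the sign reverses below that. These figures assume that control referral scales with f, that the test rate stays at 10%, 165 analysed per arm and ICC .05. They show sensitivity and do not forecast f. The caries-increment primary is unaffected.

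**What to change.** - **One definition.** Reconcile Aims, Outcomes, Sample Size and Data Analysis to the Aim 1 wording. Among children with treatment need at the baseline examination, success is care provided in primary care by 12 months without specialist referral. An untreated child is not a success. State whether absence of new caries belongs to this event or stays a separate primary. Communities are stratified on baseline caries data, so need can be set from information gathered before allocation.
- **Show the access effect.** Report managed, referred and untreated by arm, and keep the all-children analysis alongside, since prevention is also an aim.
- **Same ascertainment in both arms.** Collect referral and outside dental visits from common sources, for example items in the 12-month questionnaire that both arms complete, plus service records. Use the same data for costs.
- **Restate the planning.** The 10% vs 25% rates and the power must be recalculated for the event actually tested. Power computed for referral among children in need does not carry over to a care-provided event.

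The cost is revised outcome wording, a few questionnaire items, a records request and a restated planning figure.

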### Focus Group

A sample of parents from the randomized test and control groups will be invited to participate in focus group interviews to elicit their perspectives on the care provided to their child using the various approaches (including those referred for GA care). Children will not be involved in the focus group interviews due to their young age. Previous experience with focus group interviews indicated that a sample of about 20 from each arm of the study is sufficient to reach saturation.

The focus group questions will be based on the following:

What were some of the positive aspects of dental care your child experienced?What were some of the negative aspects of the dental care your child received?Can you give some examples of what you think could have been done/implemented better during your child’s treatment?Can you name some aspects of the setting/location/process that you think could have been improved?Can you identify any changes to your oral health knowledge since the research began?

### Sample Size

A recently completed pilot study in WA, which compared ART-based care against standard care, reported a nine-fold difference in the proportion of children referred for specialist pediatric dentist care (5% vs 49%). A conservative difference in effect size of 2.5 was assumed to estimate the sample size (10% vs 25%). The intracluster correlation was estimated from the dental caries experience of Aboriginal children participating in a NHMRC Project Grant (1010758)‒funded cluster randomized trial (.05). Using these parameters, with 15 clusters available in each arm of the trial, the estimated sample size required, at 80% power and alpha of .05, was 165 in each arm of the trial with 11 children per cluster. Allowing for loss to follow-up of 25%, the estimated sample size is 220 per arm of the study or 15 children per cluster. The recently completed pilot trial in WA, undertaken by author PA, achieved 90% retention of study participants after 12 months, while an oral health promotion intervention undertaken by author LJ among an Aboriginal population achieved 80% retention of study participants. The estimated sample size will have sufficient power to detect a 33% difference in mean ECOHIS at 90% power and alpha of .05.

The study timeline is shown in Table 2. It is expected that community engagement will take the bulk of the first year in recognition of the challenges of undertaking research in northwestern WA, which is as far as Sydney is from Perth (about 3000 km). Participant recruitment and treatment provision is similarly expected to take up to 2 years because of constraints of locations of communities and weather conditions.

**Table 2 table2:** Study timeline, indicated by actions taken per quarter.

Action	Year 1				Year 2				Year 3				Year 4				Year 5			
	1	2	3	4	1	2	3	4	1	2	3	4	1	2	3	4	1	2	3	4
Community engagement, staff recruitment, training, ethics approval, printing	✓	✓	✓	✓																
Participant recruitment, baseline, examinations, randomization, commence treatment, baseline data entry			✓	✓	✓	✓	✓	✓	✓	✓										
Follow-up examinations, focus group interviews, delayed intervention group treatments							✓	✓	✓	✓	✓	✓	✓	✓	✓					
Data entry, data clean-up, data analyses									✓	✓	✓	✓	✓	✓	✓	✓	✓			
Report preparation, community presentation and feedback																	✓	✓	✓	✓

